### Data analysis

SPSS version 25 software will be used to conduct the analyses. For all study variables, the mean and standard deviation will be presented for continuous variables, and categorical variables will be described as frequencies and percentages. No significance test will be performed because of the residual confounding that may arise from having small study groups.

Descriptive analyzes will be performed for sociodemographic and clinical variables as well as baseline maternal stress and anxiety which will be presented by study group as well as for total sample. Feasibility and acceptability variables will also be analyzed with descriptive analyses. As for maternal sensitivity to feeding cues and maternal beliefs, means will be presented by groups and effect size will be calculated using Cohen’s *d* and 95% confidence interval (CI). Regarding preterm infant neurodevelopment outcome, the GMA results will be presented as frequency of normal/abnormal for each group and the difference in proportion will be calculated. Change from baseline for maternal stress and anxiety will be compared between groups using Cohen’s *d* and 95% CI. Finally, frequency of skin-to-skin contacts, parental presence at bedside, and breastfeeding will be presented for each groups and total sample.

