**Discussion:**

Data collection for this pilot study is expected to end in 2020. Results of this pilot study will inform about the feasibility and acceptability of the study design and GP_Posit intervention, a nursing intervention having the potential to favor maternal sensitivity and infant neurodevelopment in the NICU and guide the elaboration of a large-scale RCT.

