### Sample size

A convenience sample of 20 mother-infant dyads will be recruited. It has been suggested that a minimum of 10 participants per group is sufficient for pilot studies [63, 64]. A maximum of 24 dyads could be recruited in case of attrition which is anticipated to be around 20% based on similar intervention studies [20, 31, 34, 35].

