### Randomization and allocation

An independent biostatistician of the Applied Clinical Research Unit (Unité de Recherche Clinique Appliquée (URCA)) verified the sequence of randomization as per a computer-generated random listing of interventions applying a permuted block design with random blocks of two and four. Opaque, sealed, and sequentially numbered envelopes were prepared by a professional independent from the study team. Mothers consenting to participate in the trial are randomly assigned, in a 1:1 allocation ratio, to receive either the experimental intervention or usual care. Mothers uncover their allocated group by opening the envelope in presence of the intervention nurse.

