### Protocol amendments

Since the beginning of this pilot study in late 2018, protocol amendments have been done following challenges encountered regarding recruitment. We had originally targeted a sample size of 30 (15 dyads per group) based on Julious [66] with a planned recruitment rate of two to three dyads per week. However, we initially had a recruitment rate of one dyad per month which was sub-optimal. Our solution to optimize recruitment was twofold. First, we lowered the sample size to 20 (10 dyads per group) because this sample size allowed us to estimate feasibility and acceptability. Moreover, as suggested by Leon, Davis [67], pilot studies’ sample size should be based on pragmatics such as patient flow. Second, we also made a change in inclusion criteria as we included preterm infant born between 27^0/7^ and 31^6/7^ as opposed to originally planned 28^0/7^ to 31^6/7^ WGA. Since we observed that the time needed between −*t*_1_ and *t*_1_ was of at least 1 week, preterm infants born at 27^0/7^ WGA could participate as they would be 28^0/7^ WGA by the time the experimental intervention would start.

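### Cohen's d is planned with no small-sample correction at about 10 per group; Hedges' g would remove an average overstatement of about 4.4% to 4.6% at no cost

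*Protocol article*

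**What the plan says.** The protocol article, Data analysis, fixes the effect measure for the mean-based outcomes. For maternal sensitivity and maternal beliefs, group means are to be shown and "effect size will be calculated using Cohen", with a 95% confidence interval. For the two covariates measured by questionnaire, "Change from baseline for maternal stress and anxiety will be compared between groups using Cohen", again with a 95% interval. The section also states "No significance test will be performed". So for these four outcomes d and its interval are the only between-group measure planned, beyond the group means and standard deviations. No small-sample correction is mentioned.

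The sample is small. Under Sample size: "A convenience sample of 20 mother-infant dyads will be recruited". Under Protocol amendments: "we lowered the sample size to 20 (10 dyads per group" is the stated per-group figure, and allocation is "in a 1:1 allocation ratio". An allowance for losses is made: "A maximum of 24 dyads could be recruited in case of attrition which is anticipated to be around 20" percent.

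Preliminary effects are the secondary objective; the primary objective is feasibility and acceptability. The abstract says that the results will inform on feasibility and acceptability and "guide the elaboration of a large-scale RCT".

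**The concern.** Cohen's d divides the mean difference by a standard deviation estimated from the same few participants. The reciprocal of an estimated standard deviation is too large on average, so d is too far from zero on average whenever the true effect is not zero. The exact size of the bias is known and depends only on the degrees of freedom. At about 18 degrees of freedom it is a few percent. Estimating these effects is a stated objective, and no test will be run, so the effect size itself will be what readers carry forward. A known bias that one constant removes is worth removing, even when it is small.

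**Working it through.** **Inputs from the protocol article**
- Total 20 dyads, 10 per group (Sample size; Protocol amendments), allocated 1:1 (Randomization and allocation).
- Up to 24 dyads if there is attrition, expected at about 20% (Sample size). The figure of 24 reproduces as 20 × 1.20 = 24. After a 20% loss, 24 × 0.80 = 19.2 complete, or 9.6 per group.
- Effect measure: d with a 95% interval (Data analysis).

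**Assumptions, because the article gives no figure**
- True standardised effects of 0.2, 0.5 and 0.8, shown as a range.
- Normal outcomes with equal variances. The standardiser is the pooled within-group standard deviation (for stress and anxiety, that of the change scores), so df = 2n − 2.

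**Step 1: the correction factor**

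J(df) = Γ(df/2) / [√(df/2) · Γ((df − 1)/2)], and the mean of d is δ/J.

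| Per group | df | J | Average overstatement, 1/J − 1 |
|---|---|---|---|
| 9.6 | 17.2 | 0.9556 | 4.6% |
| 10 | 18 | 0.9576 | 4.4% |

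**Step 2: absolute bias at 10 per group, δ/J − δ**
- δ = 0.2: 0.2088 − 0.2 = +0.009
- δ = 0.5: 0.5221 − 0.5 = +0.022
- δ = 0.8: 0.8354 − 0.8 = +0.035
- δ = 0: zero. The bias is multiplicative and follows the sign of each outcome's own effect.

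**Step 3: bias against random error at 10 per group**

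The standard deviation of d is about 0.48 at δ = 0.2, 0.48 at 0.5 and 0.50 at 0.8. The bias is therefore about 2% to 7% of one standard deviation (0.009/0.48 to 0.035/0.50). The noncentral-t 95% interval around an observed d of 0.5 runs from −0.40 to 1.38.

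**Step 4: what g = J × d changes at 10 per group**

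Its mean equals δ. Its standard deviation is that of d times 0.9576.

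| δ | Mean squared error of d | Mean squared error of g | Reduction |
|---|---|---|---|
| 0.2 | 0.2265 | 0.2076 | 8.3% |
| 0.5 | 0.2341 | 0.2143 | 8.5% |
| 0.8 | 0.2484 | 0.2266 | 8.8% |

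Most of this reduction comes from the smaller variance, because the squared bias is tiny.

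**The case against.** **The bias is negligible beside the random error.** This stands as a limit on importance. The bias is at most about 7% of one standard deviation of d over the assumed effects, and the planned 95% interval already shows the main uncertainty. It does not make d the better estimator. A wide interval describes random error and leaves the average shift in the point estimate in place.

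**A condensed article leaves formulas to the full protocol or analysis plan, so d may already be corrected.** This is possible, since the article gives neither a standardiser nor an interval method. But the article does name the estimator, and the usual meaning of that name is the uncorrected statistic. One word settles it.

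**Readers can convert for themselves.** This is true. Group means and standard deviations are promised for continuous variables, and g is the reported d times J. It means that nothing is lost, but it is no reason to headline the biased figure.

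**A stronger reading that the article does not support.** A reader might infer that the large trial would end up too small, by squaring the factor: 1 − 0.9576² = 8.3%. There are three reasons not to. First, the article says that the pilot will guide a large trial, and nowhere says that the trial's sample size will be computed from this d. Second, the required sample size varies as 1/d², so putting the mean of d into that formula does not give a typical planned size. At 10 per group the median of d is only about 1.4% above the true effect, while the median of g is about 2.9% below it. The chance of exceeding the true effect is about 50% to 51% with d and 48% to 49% with g. Third, random error swamps both. At an assumed true effect of 0.5, two-sided 5% and 80% power, the 10th to 90th percentiles of the planned number per arm from d are about 12 and 1,381.

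A reader might also take 8 per group as the case after attrition. That ignores the stated allowance to recruit up to 24, which leaves about 9.6 per group.

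**Conclusion.** The point holds as a minor refinement of reporting. As named, d overstates any nonzero true standardised effect by about 4.4% to 4.6% on average at the planned size: about +0.009 to +0.035 at 10 per group for assumed true effects of 0.2 to 0.8. If there is no effect, there is no bias. Hedges' g removes the average bias and lowers mean squared error by about 8% to 9%. These figures rest on normal outcomes, a pooled within-group standardiser and complete data on about 19 to 20 dyads.

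No finding on feasibility or acceptability is touched, and no reading of the preliminary effects would change. The point says nothing about the size of the later trial. Correcting the estimate does not make it fit for that use, because neither d nor g is precise enough at this sample size.

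**What to change.** In Data analysis, replace Cohen's d by Hedges' g (d multiplied by J at the achieved degrees of freedom) for maternal sensitivity, maternal beliefs, and change in stress and in anxiety. Give each a 95% interval based on the noncentral t distribution, and state the standardiser. Beside each g, report the raw mean difference with its own 95% interval. A sentence saying that these point estimates alone will not set the sample size of the main trial would forestall over-reading.

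The cost is one multiplication per outcome and a few words. No extra participants, visits or data are needed. Reported standardised effects become about 4% smaller (1 − 0.9576 = 4.2% at 10 per group; 1 − 0.9556 = 4.4% at 9.6).

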#### Control group: usual care

Mother-infant dyads allocated to the control group receive usual care. In the study NICU, nurses are thought to position the preterm infants in their incubators using specialized mattresses, but parents participating in their infant’s positioning are not a current practice. Parental participation in their infant’s care is also encouraged but it is not part of a structured practice. Finally, for all infants born before 29 WGA and whose health condition has been critical, the NICU’s physiotherapists establish a positioning care plan and meet the parents to inform them about it. Otherwise, infants with plagiocephaly or torticoli are also followed by the NICU’s physiotherapist for special positioning care plans. Because of randomization, it is expected that there will be an equivalent number of infants benefiting from this particular positioning care plan in each group.

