#### Sociodemographic and clinical data

Before randomization of dyads (−*t*_1_), sociodemographic and clinical data are collected. Maternal sociodemographic data include age, origin, ethnicity, parity, marital status, level of education, prior experience of having a preterm infant or hospitalized child, type of delivery, occupation and support received by healthcare professionals such as a psychologist, social worker, lactation consultant, or psychiatrist. Sociodemographic data regarding preterm infants include sex, gestational age at birth, birth weight, and respiratory support. Clinical data is collected only for preterm infants and includes APGAR score and SNAPPE-II score [53].

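### Maternal stress and anxiety are compared on raw change from baseline, where adjusting the t4 score for its own baseline would usually be more precise at almost no cost (low severity)

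*Protocol article*

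**What the plan says.** The Data analysis section of the protocol article names the estimator for the two maternal questionnaires: "Change from baseline for maternal stress and anxiety will be compared between groups using Cohen"'s *d*, with a 95% CI. It mentions no baseline covariate. The only other use it gives the pre-randomisation scores is descriptive: "baseline maternal stress and anxiety which will be presented by study group as well as for total sample".

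The scores needed for adjustment exist. Participant timeline has mothers completing questionnaires after consent and before allocation, and again at t4 (36 WGA). Other confounding variables names PSS:NICU and STAI as the instruments.

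Data analysis also explains why there are no p-values: "No significance test will be performed because of the residual confounding that may arise from having small study groups". Sample size sets 20 dyads, with up to 24 if there is attrition, and Randomization and allocation sets a 1:1 ratio.

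**The concern.** Subtracting the baseline assumes that a mother who starts one unit higher will, without any effect, finish one unit higher. When the correlation between the two times is below 1 and the SDs are similar, the expected difference at t4 is smaller than that, so subtraction over-corrects. This has two consequences in a small trial. The estimate is noisier than it needs to be. And a chance difference between arms at baseline returns, with opposite sign, as an apparent difference in change.

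The plan is worried about imbalance in small groups, but what it does about it misses the mark. Chance imbalance after randomisation is not residual confounding. Leaving out the p-value does not reduce it either, because the same imbalance sits in the *d* and the interval that are still reported. Imprecision is a sound reason not to test.

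At stake is the quality of two descriptive effect estimates, not the validity of the trial.

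**Working it through.** **Inputs.** N = 20, 10 per arm (Sample size; Protocol amendments), 1:1 allocation. The documents give no SD and no baseline-to-t4 correlation for either questionnaire. I therefore work in SD units, assume equal SDs at both times, and show a range of rho. There is no stated figure on this point to reproduce. The nearest, the maximum of 24 dyads, follows from 20 × 1.2 and is not in dispute.

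**Variance of the between-arm difference, relative to t4 alone (= 1).**
- Change score: 2(1 − rho).
- ANCOVA: (1 − rho²) × (1 + 1/(N − 4)). At N = 20 the last factor is 17/16, the small-sample price of one covariate.
- Ratio of ANCOVA to change: (1 + rho)/2 × 17/16.

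| assumed rho | change | ANCOVA | ratio | 95% CI half-width, change | 95% CI half-width, ANCOVA |
|---|---|---|---|---|---|
| 0.3 | 1.400 | 0.967 | 0.69 | 1.11 SD | 0.93 SD |
| 0.5 | 1.000 | 0.797 | 0.80 | 0.94 SD | 0.84 SD |
| 0.7 | 0.600 | 0.542 | 0.90 | 0.73 SD | 0.69 SD |
| 0.8 | 0.400 | 0.382 | 0.96 | 0.59 SD | 0.58 SD |

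The variance reductions are thus 31%, 20% and 10% at rho 0.3, 0.5 and 0.7. Half-widths are t × √(2/10) × √(relative variance), with 18 df for change and 17 df for ANCOVA.

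**Break-even.** (1 + rho)/2 × 17/16 = 1 gives rho = 15/17 = 0.88. With 24 dyads the factor is 21/20 and the break-even is 19/21 = 0.90. With 16 it is 13/12 and 11/13 = 0.85. Below rho = 0.5 the change score is also noisier than ignoring the baseline altogether, since 2(1 − rho) then exceeds 1.

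**Chance imbalance.** The baseline difference between arms has SD √(2/10) = 0.447 SD. The probability that it is at least 0.5 SD in either direction is P(|Z| ≥ 0.5/0.447) = 0.26. With no true effect and an imbalance of δ, the change score has expected error −(1 − rho)δ. For δ = 0.5 this is −0.35, −0.25 and −0.15 SD at rho 0.3, 0.5 and 0.7. ANCOVA has expected error 0.

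**Simulation check** (40,000 trials, 10 per arm). Among trials with an imbalance near 0.5 SD, the change score was off by −0.34, −0.24 and −0.15 SD, and ANCOVA by less than 0.01 SD. At rho 0.5 the variances were 0.200 for change and 0.158 for ANCOVA. Averaged over all randomisations, both estimators were centred on the truth.

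**The case against.** Five points can be made against this.

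1. **Stress and anxiety are not among the outcomes of the secondary objective.** That objective lists sensitivity, beliefs, EEG synchrony and general movements; PSS:NICU and STAI sit under Other confounding variables. This stands, and it is the main reason for low severity.

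2. **The gain depends on an unknown correlation and changes little in practice.** This stands in part. At rho 0.8 the gain is about 5%, and at rho 0.5 the interval is still ±0.84 SD. But the gain is positive over most of the range and costs nothing to collect.

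3. **Covariate adjustment is usually left to a fuller document, and the protocol presents baseline data by group, so imbalance will be visible.** This protects the plan against a complaint about silence. It does not cover the point here, because the article names the change score as its estimator.

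4. **A reader might infer that the other effect estimates are also too noisy for want of adjustment.** For sensitivity and beliefs, "means will be presented by groups and effect size will be calculated using Cohen"'s *d*; for general movements, "the difference in proportion will be calculated". The documents do not support that inference. These outcomes are described only at t4, so they have no baseline of their own. Gestational age at birth is collected, but adjusting for it at N = 20 gains precision only if (1 − rho²) × 17/16 < 1, that is, if its correlation with the outcome exceeds √(1/17) = 0.24. No such correlation is given, and eligibility narrows the range to 27 0/7 to 31 6/7 WGA.

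5. **A reader might also infer an error in the usual-care section, where "it is expected that there will be an equivalent number of infants benefiting from this particular positioning care plan in each group".** That does not hold up either. The care plan goes to infants born before 29 WGA whose condition has also been critical, and separately to those with plagiocephaly or torticollis. The documents give no frequency for it, and the sentence states an expectation, which randomisation does provide on average.

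**Conclusion.** The point holds for PSS:NICU and STAI. The protocol fixes a less precise estimator than its own data allow for any baseline-to-t4 correlation below about 0.88, and that estimator passes chance baseline imbalance into the result. This rests on equal SDs at both times, about 10 dyads per arm and an assumed rho. The change score should not be called biased: it is unbiased over randomisations, and the fault is lost precision together with error conditional on the imbalance that happens to occur. The reason given for omitting significance tests is also mislabelled, although the decision not to test is sound. Severity is low, because the trial is a feasibility pilot, its effects are described as preliminary, and these two measures are not among its listed outcomes.

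**What to change.** - **Estimator.** In Data analysis, replace the change-score comparison for PSS:NICU and STAI with the t4 mean difference between arms adjusted for the measure's own baseline (ANCOVA: t4 score on arm plus baseline), with its 95% CI. If a standardised effect is wanted, divide by a named SD, such as the pooled baseline SD.
- **Rationale.** Give imprecision with small groups, not residual confounding, as the reason for performing no significance tests.
- **Optional.** A gestational-age-adjusted estimate for sensitivity and beliefs may be shown beside the unadjusted *d* as a sensitivity analysis, with no claim that it is more precise. Skin-to-skin contact, parental presence and breastfeeding arise after randomisation and should not be used as adjustment covariates.

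The cost is a change of wording and one degree of freedom per model. No extra dyads or data are needed.

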#### Exploratory analyses

EEG data is recorded mainly to assess the feasibility of using the 8-electrode portable device with hospitalized preterm infants as well as parent’s acceptability of performing this test for research purposes. Additional exploratory analyses will be performed on recorded EEG data. We will perform spectral analyses with multiscale entropy calculation and connectivity analyses in order to see synchrony using the phase slope index [65]. According to Bastos and Schoffelen [65], this should allow us to study the dynamic connections between neuronal populations.

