#### Secondary objective

The secondary objective is to estimate the preliminary effects of GP_Posit on mothers and preterm infants’ outcomes. The specific question leading this study is : what are the preliminary effects of the GP_Posit intervention, compared to standard care, at the primary endpoint (when preterm infants will have reached 36 weeks of gestational age (WGA)) on:
(Q1) Maternal sensitivity score to their preterm infant’s cues during oral feeding.(Q2) Maternal beliefs about their preterm infant’s needs and their maternal role in the NICU.(Q3) Preterm infant cerebral activity synchrony during eyes-closed electroencephalogram.(Q4) Preterm infant will have better quality of general movements.

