**Feasibility of the design**		
Recruitment	What is the number of dyads that were recruited compared to the number of dyads that were evaluated for eligibility?	Number of recruited mothers/mothers evaluated for eligibility.
	What are the characteristics of participating dyads?	Sociodemographic data.
	How much time is needed to reach sample size?	Time needed to reach sample size.
Randomization	Is the method of randomization feasible?	Number of non-eligible participants randomized.
Measure methods	Feasible to use EEG to measure neurodevelopment?	Number of EEGs performed.
Data collection	Is it feasible to perform data collection as planned?	% of data collection performed as planned.
Retention	Are we able to retain all dyads throughout the study?	Number of lost to follow-up and reason.
Contamination	Is there a risk of contamination?	% of mothers that were exposed to the content of the intervention.

**Table 2 Tab2:** Indicators of acceptability

Elements	Question	Indicators

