**Acceptability of design**		
Recruitment	Do the eligible mothers accept to participate?	% of eligible mothers that participate.
Randomisation	Do the mothers accept to be randomized?	Reason of refusal.
Data collection	Is it acceptable for mothers that we perform EEGs to their preterm infant?	80% of mothers accept.
	Is it acceptable for mothers that we perform the GMA to their preterm infant?	80% of mothers accept.
	Is it acceptable for mothers to be filmed while they breastfeed or bottle-feed?	80% of mothers accept.
	Is it acceptable for mothers to complete questionnaires?	80% of mothers accept.
General acceptability of the intervention^a^	Is it acceptable for mothers to participate in their infant’s positioning?	80% of mothers find it acceptable.
	Is it acceptable for mothers to participate in 30–45 min. intervention sessions, once to twice per week, throughout the hospitalization?	80% of mothers find it acceptable.
Appreciation^a^	Were mothers satisfied by the intervention?	80% of mothers were satisfied.
	Did mothers find it easy to participate?	80% of mothers found it easy.
	Did mothers find it challenging to participate?	Challenges encountered.
	Did the mothers find the intervention useful?	80% of mothers found it useful.
Retention^a^	Which strategies could enhance retention?	Suggested strategies by mothers.

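### The phase slope index measures which EEG channel leads, so a group contrast in it does not answer the synchrony question (Q3)

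*Protocol article*

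**What the plan says.** Under Secondary objective, Q3 asks for the preliminary effect of GP_Posit, compared with standard care, at 36 weeks of gestational age on "Preterm infant cerebral activity synchrony during eyes-closed electroencephalogram".

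Under Other outcomes, the article says only that connectivity analyses will follow an 8-probe resting-state recording. Exploratory analyses names the statistic: "connectivity analyses in order to see synchrony using the phase slope index". The same section says "We will perform spectral analyses with multiscale entropy calculation", but does not tie spectral analysis or entropy to synchrony. No other synchrony statistic is named.

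On purpose, Exploratory analyses states that "EEG data is recorded mainly to assess the feasibility of using the 8-electrode portable device with hospitalized preterm infants", together with acceptability to parents. In Table 1 the matching question is "Feasible to use EEG to measure neurodevelopment", and its indicator is "Number of EEGs performed". A separate row of Table 1 gives the percentage "of data collection performed as planned". Table 2 asks "Is it acceptable for mothers that we perform EEGs to their preterm infant" and sets an 80% criterion for it.

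**The concern.** Synchrony is a symmetric property of two signals: how consistently they move together, whichever is named first. The phase slope index describes something else, namely whether one channel systematically precedes the other. If it is reported under Q3, two errors become possible. A real group difference in zero-lag or mutual coupling could leave the index unchanged. A group difference in direction or lag of flow could be reported as a difference in synchrony. Either would pass a mislabelled EEG result to the large-scale trial that this pilot is meant to inform.

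A smaller point concerns feasibility. Table 1 asks whether EEG can be used to measure neurodevelopment, and the number of recordings made does not by itself show that.

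**Working it through.** The article gives no figure for the EEG measures, so there is none to reproduce. The check starts from the definition of the index. Sampling rate, recording length, frequency band and noise level below are assumptions, because the article states none of them for the analysis.

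**Definition.** With C(f) the complex coherency of two channels, PSI = Im[ Σ C*(f) · C(f + Δf) ], summed over the band (unnormalised).

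- Zero lag: C(f) is real, so every product is real and PSI = 0.
- Balanced two-way coupling: the two delays contribute conjugate terms, C(f) is again real, and PSI = 0.
- Phase offset constant over frequency: the phase does not change from f to f + Δf, so PSI = 0.
- Swapped channels: C becomes C*, and PSI changes sign.
- Pure lag τ with coherence magnitude c: each product contributes c² · sin(2πΔf·τ), so PSI depends on the lag as well as on the strength of coupling.

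**First simulation** (256 Hz, 10 min, 2-s Hann windows, 1–20 Hz):

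| Signal pair | Coherence | Phase-locking value | PSI |
|---|---|---|---|
| Identical | 1.00 | 1.00 | 0.000 |
| Constant 90-degree offset | 1.00 | 1.00 | 0.000 |
| Zero lag, small noise | 0.92 | 0.85 | 0.011 (SD 0.022) |
| Zero lag, more noise | 0.50 | 0.41 | 0.002 (SD 0.022) |
| Independent | 0.04 | 0.01 | 0.002 (SD 0.005) |
| 20 ms lag | 0.50 | 0.32 | +0.585 |
| 20 ms lag, channels swapped | 0.50 | 0.32 | −0.585 |

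The lagged value can be confirmed by hand. Two-second windows give Δf = 0.5 Hz and 38 products from 1 Hz to just below 20 Hz. The lag is 5/256 = 0.0195 s. So PSI = 38 × 0.501² × sin(2π × 0.5 × 0.0195) = 38 × 0.251 × 0.0613 = 0.585. At zero lag the sine is zero.

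The spread around zero is wider for coupled than for independent pairs (SD 0.022 against 0.005), but that is estimation noise. The means do not separate.

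**Second simulation** (250 Hz, 5 min, 2-s windows, 4–20 Hz, 30 replicates), adding two-way coupling and the weighted phase-lag index:

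| Signal pair | Coherence | PSI | Weighted phase-lag index |
|---|---|---|---|
| Zero lag | 0.80 | −0.02 (SD 0.04) | 0.068 |
| Balanced two-way | 0.43 | 0.00 (SD 0.05) | 0.070 |
| Independent | 0.07 | 0.01 (SD 0.03) | 0.071 |
| One-way lag | 0.80 | 1.28 (absolute) | 0.95 |

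A repeat run put the weighted phase-lag index at about 0.09 for the first three pairs and again 0.95 for the last. It therefore misses the same two forms of coupling as the phase slope index.

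**Count of EEGs.** Participant timeline places an EEG before randomization and another at 36 weeks. With 20 dyads of one infant each, 20 × 2 = 40 are due; the eligibility criteria allow more than one infant per mother, which would raise this. If all 40 are performed, the count reads 40 whether 20, 28 or 36 are analysable (assumed shares of 50%, 70% and 90%). The article gives no share.

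**The case against.** The strongest reply is that insensitivity to zero lag can be deliberate. One source reaching two electrodes also produces zero-lag coupling, and coherence and phase-locking value cannot tell the two apart. This stands. A reader might infer from the zero values that the phase slope index is a faulty statistic; the check does not support that. The index is valid for direction, and the error lies in assigning it to synchrony.

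The second reply is that little rests on the result. The section is headed exploratory, Data analysis rules out significance tests, and about 20 dyads are described. This also stands, and it limits the weight. It does not remove the mismatch, because a descriptive contrast would still be presented under Q3.

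The third reply concerns feasibility. A reader might infer that EEG completion has no denominator, or that EEG could be declared feasible on unusable recordings. The article does not support either reading. Table 1 separately reports the percentage of data collection done as planned, no decision threshold attaches to the EEG count, and the stated feasibility criterion is attendance at four or more sessions by at least 80% of mothers. Rules on artefact-free length are details that an article may leave to the full protocol. What remains is that neither the count nor the completion rate reflects whether a recording can be analysed, which is what the Table 1 question turns on.

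Nor is it true that none of the EEG measures fits its question: acceptability to mothers has its own matching 80% criterion.

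**Conclusion.** The point holds for Q3. The only statistic the article assigns to synchrony measures direction. Its expectation is the same for strong zero-lag coupling, balanced two-way coupling and no coupling, yet it moves from about 0 to 1.28 between two pairs that share a coherence of 0.80. The zero results follow from the definition and do not depend on the simulation settings; the non-zero values do.

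The importance is low: the analysis is exploratory and descriptive, and no trial decision depends on it. The feasibility remark is a minor addition. Its only figures, 20, 28 or 36 analysable out of 40, rest on assumed shares and one infant per dyad.

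**What to change.** - **Q3:** name a symmetric measure, coherence or phase-locking value, computed from the same recordings. State that it cannot separate zero-lag coupling from volume conduction. Keep the phase slope index as a separate description of direction. The alternative is to reword Q3 as directed connectivity and leave the index as it is.
- **Weighted phase-lag index:** add it, if wanted, only as a sensitivity measure of lagged coupling. It should not stand as the synchrony measure.
- **Table 1:** beside the number of EEGs performed, report the number analysable over the number due (two per infant), by a criterion fixed before the recordings are reviewed.

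The cost is wording and a modest amount of extra analysis; no new recordings are needed. The EEG feasibility figure may look less favourable, and the synchrony result will carry the volume-conduction caveat.
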